### Participant timeline

The participant timeline of assessments is summarized below (Fig 2):

#### Enrollment and baseline

Potential participants will be screened to determine if they meet the eligibility criteria. Potential participants who meet the eligibility criteria will be approached by a trial coordinator to determine if they agree to participate. If they agree, they will be asked to and sign the PICF. Once the PICF is signed, they will be considered enrolled, and the participant will be randomized, asked to complete the Trial Health Questionnaire and be provided a Study Diary.

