#### Follow-up assessment

Follow-up will occur at weeks 3, 7, and 12; then months 6, 12, 18, and 24; and then years 3, 4, and 5 from the date of hospital discharge. All follow-up assessments, except for the 7-week, will take place in the hospital clinic at the time of the participant’s routine follow-up visits with the surgeon. The trial coordinator will be available to assist the participant in completion of the Trial Health Questionnaire as well as review the Study Diary with the participant. At the 7-week trial follow-up assessment, the trial coordinator will collect the data over the telephone. Five-year survival data will also be obtained by conducting a quick chart review at five-years. The patients have routine surveillance follow-up appointments with the surgeon every 6 or 12 months after surgery, either in-person or virtually, so survival data will be available from the surgeon’s surveillance follow-up note at five years.

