### Concealment mechanism

All participants who provide consent for participation and who fulfil all eligibility criteria will be randomized. Participants will be randomized using the central web-based Research Electronic Data Capture (REDCap) [15] randomization module. A statistician not otherwise involved with the trial will generate the randomization sequence and upload it into the REDCap randomization module. The module sequentially assigns participants to treatment groups and monitors the progress of allocation. The randomization sequence and blocking information will be concealed from all trial staff including the principal investigator, the biostatistician, and trial coordinators until the database is closed.

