### Implementation

The trial coordinator will enroll participants in the trial. Once a participant is enrolled, the trial coordinator will access REDCap to randomize participants to either VATS-Lobectomy or RTS-Lobectomy. After a participant has been randomized, the allocation information will be stored in the database and will not be able to be modified.

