## Assignment of interventions: Blinding

### Who will be blinded

As this is a surgical trial, provider blinding will not be feasible. Participants will remain blinded to the type of surgery they receive from the time of enrollment until the end of the trial follow-up period, at which time the trial coordinator will inform the participant as to which intervention they were randomized to (VATS-Lobectomy or RTS-Lobectomy). The operating room setup and resulting scars from both surgical procedures are comparable and should not compromise participant blinding. The biostatistician performing the analysis will be blinded as to which intervention arm participants were allocated to as the group allocations will be coded as Group A and Group B. To reduce observer bias, the trial coordinator (outcome assessor) will only provide minimal assistance (e.g., reading a question) to participants while they are completing their self-reported Trial Health Questionnaire.

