#### Baseline data collection

Baseline data including demographics (e.g., age, BMI, gender), medical history (e.g., smoking, alcohol use, comorbidities, analgesia consumption, pain, previous thoracic surgery, previous cancer), tumour characteristics (e.g., clinical stage, histology), and physiology (e.g., pulmonary function) will be collected. In addition, participants will be asked to complete the Trial Health Questionnaire and they will be provided with a Study Diary.

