#### Trial health questionnaire

The Trial Health Questionnaire includes questions on the participant’s employment status, social activities (e.g., smoking, alcohol use), pain assessment (Numeric Pain Rating Scale) and two surveys, the EQ-5D-5L [16] and the Reintegration to Normal Living Index (RNLI) [17].

The NPRS is a numeric version of the visual analog scale, with 0 representing no pain and 10 representing the worst pain the participants can imagine. Participants will be asked to indicate their pain on movement (deep breathing or mobilization). The EQ-5D-5L has been validated for a number of chronic conditions, including cardiovascular and respiratory disease. The EQ-5D-5L is comprised of a descriptive system as well as a visual analog scale that assesses dimensions related to mobility, self-care, usual activities, pain/discomfort, and anxiety/depression. Respondents are asked to report their health states by rating each dimension as one of five levels (no problems, slight problems, moderate problems, severe problems and extreme problems). The RNLI is a self-report questionnaire used to evaluate global function status of a patient during rehabilitation which was developed to qualitatively assess the ability of individuals with traumatic or incapacitating illnesses to reintegrate into normal life. The RNLI is a questionnaire that is comprised of 11 questions that assesses mobility, self-care, daily activity, recreational activity, and family roles. Reintegration to normal living was defined as the reorganization of physical, psychological, and social characteristics of an individual into a harmonious whole so that one can resume well-adjusted living after incapacitating illness or trauma [18]. Each domain contains a visual analogue scale. On one end: “does not describe my situation” (1 or minimal integration) and “fully describes my situation” (10 or complete integration). Individual item scores are summed to provide the total score. The higher the score, the better the patients perceived integration.

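### The protocol as written places the baseline questionnaire after randomization, when the coordinator who may assist already knows the arm: a small, easily removed risk

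*Protocol article*

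**What the plan says.** Under Participant timeline, Enrollment and baseline, signing the consent form makes a person enrolled, and then "the participant will be randomized, asked to complete the Trial Health Questionnaire and be provided a Study Diary". The COVID-19 procedure in the same section also moves from consent to enrollment to randomization and does not mention the questionnaire. Under Implementation: "Once a participant is enrolled, the trial coordinator will access REDCap to randomize participants".

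The Trial Health Questionnaire contains the pain rating, the EQ-5D-5L and the RNLI (Trial health questionnaire). Baseline data collection lists it among the baseline items without placing it before or after allocation: "In addition, participants will be asked to complete the Trial Health Questionnaire and they will be provided with a Study Diary".

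On who knows what, Concealment mechanism says "The randomization sequence and blocking information will be concealed from all trial staff including the principal investigator, the biostatistician, and trial coordinators". This concealment ends at database closure. Who will be blinded states that participants are blinded from enrollment to the end of follow-up, and that "the trial coordinator (outcome assessor) will only provide minimal assistance (e.g., reading a question) to participants while they are completing their self-reported Trial Health Questionnaire".

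**The concern.** A baseline measurement is safest when nobody involved in taking it can know the arm. Completing the questionnaire before randomization guarantees this; completing it afterwards leaves it to other safeguards. Here the person who has just made the allocation is also the person who may help with the form.

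Two things are at stake. First, baseline utility is the presumable starting point of the QALY area under the curve, a possible time point in the repeated-measures analysis, and an obvious candidate for adjustment in regression. A baseline value influenced by allocation could carry a distortion into any of these. Second, a participant who leaves after randomization but before the questionnaire belongs to the intention-to-treat set with no baseline value.

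**Working it through.** No figure in the plan is disputed, so the check is mainly of the text.

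**1. Order of the steps**
- Abstract, Methods: randomization follows consent.
- Enrollment and baseline: consent, randomization, questionnaire, diary, in that order.
- COVID-19 procedure: consent, enrollment, randomization; questionnaire not mentioned.
- Implementation: randomization once enrolled.
- Baseline data collection: questionnaire listed, no timing against randomization.

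The one place that lists both steps puts randomization first, and no text shown puts the questionnaire first. The schedule of assessments (Fig 2) is not shown.

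**2. Who knows the arm**
- The coordinator randomizes: "the trial coordinator will access REDCap to randomize participants to either VATS-Lobectomy or RTS-Lobectomy".
- What is concealed from coordinators is the sequence and the blocking, not an assignment already made.
- The coordinator later tells participants which operation they were allocated to (Procedure for unblinding if needed).

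The coordinator is therefore not blinded. The participant is.

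**3. How knowledge could reach the answers**
The form is self-reported by a blinded person who has not yet been operated on. The only route is the coordinator's help, which is limited to minimal assistance. That sentence is general, so help at baseline is permitted but not specifically described.

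**4. Which analyses use baseline**
- Week-12 t-test or Wilcoxon rank-sum test, unadjusted: not used, so unaffected.
- Regression: affected only if baseline utility is a covariate. The article names no covariates.
- Repeated-measures ANOVA: affected only as far as baseline is included.
- QALY by area under the curve: affected through the first interval, assuming that the curve starts at baseline.

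**5. Whether a size can be given**
Let d be the difference between arms in mean baseline utility caused by knowledge of allocation, and b the slope of the outcome on baseline.
- Baseline-adjusted effect: it moves by b × d, in the direction opposite to d.
- Unadjusted QALY difference: it moves by d × T / 2, where T is the first interval in years (trapezoid rule).

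The documents give neither d nor b, and the article does not fix T. With assumed ranges of d = 0.01 to 0.03 and b = 0.3 to 0.7, the adjusted effect moves by 0.3 × 0.01 = 0.003 to 0.7 × 0.03 = 0.021. With T assumed to be 3 to 12 weeks, the QALY difference moves by 0.01 × (3/52) / 2 = 0.0003 to 0.03 × (12/52) / 2 = 0.0035. The first range is sevenfold and the second about twelvefold. Both follow wholly from the assumptions, and nothing in the documents shows that d differs from zero. They show how the mechanism works and are not estimates.

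**6. Missing baseline values**
An allocation cannot be modified once stored (Implementation). Participants who withdraw after randomization keep their data in the trial unless they ask otherwise (Plans to promote participant retention and complete follow-up). All randomized participants are analysed, with multiple imputation for the primary outcome only. Someone who withdraws between the two steps is therefore in the analysis set with no baseline utility to inform imputation. The article does not say how far apart the steps are, so the number cannot be given.

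**The case against.** The strongest reply is that the protocol already deals with the mechanism. The respondent is blinded from enrollment, answers for herself or himself, and has no scar or recovery to reveal the arm. The coordinator's help is restricted expressly to reduce observer bias. This largely stands, and it is why the risk is small.

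A second reply is that the sentence under Enrollment and baseline may be a loose list in a condensed article, with practice already running the other way. That is possible. It does not remove the point, because no text shown states the safer order.

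A third is that withdrawal between two steps at the same contact must be rare. If they do fall at one contact, that is right.

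Some stronger readings are tempting but not supported:
- *The baseline is unprotected.* This ignores participant blinding and the limit on help.
- *The primary result is biased.* No baseline adjustment is named, and an unadjusted week-12 comparison does not use baseline. The covariate list may properly sit in an analysis plan that is not shown.
- *The coordinator is described as helping at baseline.* The sentence about the coordinator's availability to assist, under Follow-up assessment, concerns visits after discharge only.
- *Allocation concealment fails.* Enrollment precedes allocation and the sequence is concealed; the order of the questionnaire does not change that.

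**Conclusion.** The point holds as a minor one about the order of procedures. On the written text, baseline EQ-5D-5L, pain and RNLI are collected after allocation, at a time when an unblinded coordinator may give minimal help. The resulting bias is probably small and cannot be quantified from the documents. It could touch the start of the QALY curve, the repeated-measures analysis and any baseline-adjusted regression, but not an unadjusted week-12 comparison. No sample size changes.

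This rests on reading the list under Enrollment and baseline as a sequence, on applying the general sentence about assistance to the baseline visit, and on the QALY curve starting at baseline. Trial status reports Phase A as almost complete, so a change now mainly benefits Phase B. The Phase B target exceeds that of Phase A by 592 − 186 = 406 participants; how many of these are still to be recruited is not stated.

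**What to change.** In Enrollment and baseline, including its COVID-19 procedure, state that the participant completes the Trial Health Questionnaire after consent and before the coordinator opens the REDCap randomization module. Align Implementation with this. Make a completed baseline form a REDCap precondition for randomizing all further participants. For those already randomized, record which step came first where this is known, so that the analysts can describe it.

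If practice already follows this order, the cost is a sentence. Otherwise two steps are reordered and one database rule is added, with no extra visit or staff. Recording the order for earlier participants needs a check of existing records.

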**Fig 2 pone.0261767.g002:**
[figure not shown]
Schedule of assessments and evaluations.

During the COVID-19 pandemic, the potential participants who have given permission to the PI to be contacted by a member of the research team, and who meet the eligibility criteria, will be approached via phone to determine if they agree to participate. If the potential participants have an email address, then the PICF will be emailed to them. The entire PICF will be reviewed and discussed. If they agree, they will be asked if they have a printer and scanner, so that the emailed PICF can be printed, signed, scanned, and emailed back to the research team. If they do have all of the listed items, then they will provide written consent. If they do not have all of the listed items, then they will provide verbal consent. Once either written or verbal consent is provided, they will be considered enrolled and then randomized. The consent discussion information will be recorded on the Consent Discussion Form.

#### Hospital stay

The participant will be admitted to the hospital and they will have the intervention they were randomized to. Intravenous patient-controlled analgesia will be administered to all patients in the hospital postoperative period, and managed by the hospital’s pain service. Prior to discharge, participants will complete the Trial Health Questionnaire.

#### Follow-up assessment

Follow-up will occur at weeks 3, 7, and 12; then months 6, 12, 18, and 24; and then years 3, 4, and 5 from the date of hospital discharge. All follow-up assessments, except for the 7-week, will take place in the hospital clinic at the time of the participant’s routine follow-up visits with the surgeon. The trial coordinator will be available to assist the participant in completion of the Trial Health Questionnaire as well as review the Study Diary with the participant. At the 7-week trial follow-up assessment, the trial coordinator will collect the data over the telephone. Five-year survival data will also be obtained by conducting a quick chart review at five-years. The patients have routine surveillance follow-up appointments with the surgeon every 6 or 12 months after surgery, either in-person or virtually, so survival data will be available from the surgeon’s surveillance follow-up note at five years.

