**Methods:**

The RAVAL trial will be conducted in two phases: Phase A will enroll 186 early-stage non-small cell lung cancer patients who are candidates for minimally invasive pulmonary lobectomy; while Phase B will continue to recruit until 592 patients are enrolled. After consent, participants will be randomized in a 1:1 ratio to either robotic- or video-assisted lobectomy, and blinded to the type of surgery they are allocated to. Health-related quality of life questionnaires will be administered at baseline, postoperative day 1, weeks 3, 7, 12, months 6, 12, 18, 24, and years 3, 4, 5. The primary objective of the RAVAL trial is to determine the difference in patient-reported health-related quality of life outcomes between the robotic- and video-assisted lobectomy groups at 12 weeks. Secondary objectives include determining the differences in cost-effectiveness, and in the 5-year survival data between the two arms. The results of the primary objective will be reported once Phase A has completed accrual and the 12-month follow-ups are completed. The results of the secondary objectives will be reported once Phase B has completed accrual and the 5-year follow-ups are completed.

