### Objectives

#### Primary objective

Phase A of this trial is intended to determine the difference in patient-reported HRQOL outcomes between RTS-Lobectomy and VATS-Lobectomy at 12 weeks post-surgery. We hypothesize that for patients with early-stage non-small cell lung cancer (NSCLC), RTS-Lobectomy results in improved patient-reported quality of life as compared to VATS-Lobectomy.

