#### Secondary objectives

In Phase A of this trial, we will compare differences in short-term clinical outcomes, and HRQOL outcomes at weeks 3 and 7; and months 6 and 12, which coincide with the intervals of oncological surveillance. We will also compute resource utilization and calculate the incremental cost effectiveness between RTS-Lobectomy and VATS-Lobectomy.

In Phase B of this trial, we will compare the difference in the 5-year survival data between the two arms. We will also compare differences in HRQOL outcomes at months 18 and 24; and years 3, 4, and 5, which coincide with the intervals of oncological surveillance. We will also compute resource utilization and calculate the incremental cost effectiveness between RTS-Lobectomy and VATS-Lobectomy.

RTS-Lobectomy is a new technology that has not been studied extensively yet against VATS-Lobectomy, so equipoise still exists. However, based on preliminary data from our experience and from literature, we hypothesize that for short-term clinical outcomes, RTS-Lobectomy leads to higher quality pathological staging by improved lymphadenectomy, and is associated with shorter duration of chest tube drainage; shorter hospital length of stay; less intraoperative blood loss; lower postoperative analgesia requirements; and less chronic postsurgical pain as compared to those who receive VATS-Lobectomy.

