### Outcomes

#### Primary outcome

The primary outcome is difference in HRQOL scores between the treatment groups, as measured by the EQ-5D-5L questionnaire at week 12.

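### The primary objective sets HRQOL at 12 weeks after surgery, but visits are scheduled from hospital discharge, which the trial expects to come earlier with RTS; the expected bias is small and the fix is cheap.

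*Protocol article*

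**What the plan says.** The primary objective of Phase A is the "difference in patient-reported HRQOL outcomes between RTS-Lobectomy and VATS-Lobectomy at 12 weeks post-surgery". The Primary outcome section repeats the time point without an origin: the difference in scores "as measured by the EQ-5D-5L questionnaire at week 12".

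The Follow-up assessment section does name an origin. One sentence begins "Follow-up will occur at weeks 3, 7, and 12; then months 6, 12, 18, and 24" and ends "years 3, 4, and 5 from the date of hospital discharge", so the discharge origin covers week 12 as well as the later visits. The same section places every visit except week 7 at routine surgical follow-up, and describes routine surveillance as running at 6- or 12-month intervals after surgery.

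Two other statements matter. Under Enrollment and baseline, participants are randomized once consent is signed, before admission. The Secondary objectives list "shorter hospital length of stay" among the expected advantages of RTS, and the Secondary analysis section and Table 3 repeat that hypothesis.

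**The concern.** The article states both origins and nothing in its text reconciles them. This is a contradiction on the primary time point, not a detail left to a fuller protocol or an analysis plan.

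The choice of origin also matters in principle. The surgery date does not depend on how long the patient stays afterwards; the discharge date does. If the length-of-stay hypothesis is right, VATS patients, and patients with complications in either arm, complete each questionnaire later after surgery. While utility is still recovering, those extra days raise their scores, which works against RTS. The comparison would then be made at the same time since leaving hospital but at different times since the operation, which is not what the primary objective describes.

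**Working it through.** **1. The plan's own figure.** Inputs from the Sample size section: MID 0.07, SD 0.16, 80% power, significance level 0.05 (read as two-sided), 10% dropout.

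- n per arm = 2 × (1.960 + 0.842)² × 0.16² / 0.07² = 82.04, rounded up to 83. The t-test solution is 82.98, also 83. Total 166.
- Power at 83 per arm is 0.805.
- Dropout: 83 / 0.90 = 92.2, rounded up to 93 per arm, 186 in all.
- A one-sided test would need 65 per arm, so the stated figure is two-sided.

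The sample size reproduces and this point does not challenge it. The MID and SD serve below as the yardstick.

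**2. Where the week-12 score falls.** Days since surgery = 84 + postoperative stay.

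| Source of stay in the article | RTS | VATS | Week-12 day, RTS | Week-12 day, VATS | Gap |
|---|---|---|---|---|---|
| Matched database comparison (Background), 5.9 vs 6.3 days | 5.9 | 6.3 | 89.9 | 90.3 | 0.4 day |
| The group's own medians (Background), 4 vs 4 days | 4 | 4 | 88 | 88 | 0 |

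The score is therefore about 4 to 6 days past 12 weeks after surgery in both arms. The spread given for the group's RTS series, 3 to 6 days, corresponds to days 87 to 90. The gap between arms is 0 to 0.4 day, at most 0.4 / 84 = 0.5% of the interval at week 12 and 0.4 / 21 = 1.9% at week 3.

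**3. Bias at week 3.** Bias = gap × slope of recovery. The documents give no slope. I assume 0.003 to 0.007 utility per day.

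- Gap 0: bias 0.
- Gap 0.4 day: 0.4 × 0.003 = 0.0012; 0.4 × 0.007 = 0.0028.
- Against the MID: 0.0012 / 0.07 = 1.7%; 0.0028 / 0.07 = 4.0%.

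**4. Bias at week 12.** Recovery should be flatter by then. I assume 0.005 to 0.02 utility per week, also not from the documents.

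- Gap 0.4 day: (0.4 / 7) × 0.005 = 0.0003; (0.4 / 7) × 0.02 = 0.0011. That is 0.4% to 1.6% of the MID.
- If the true difference is 0.07 and the observed difference is reduced by that bias, power at 83 per arm goes from 0.805 to between 0.80 and 0.79.
- For scale only, an assumed gap of 1 day gives 0.0007 to 0.0029 (1% to 4% of the MID) and power of 0.80 to 0.77.

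**5. Limit of the inputs.** The article measures stay from admission to discharge and does not define it for the cited series. Postoperative stay, which is what shifts the visit, may be slightly shorter.

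**The case against.** The strongest reply is that the numerical effect is close to nil. On the article's own stays the arms differ by less than half a day, the direction is conservative for a hypothesis of RTS superiority, and clinic visits may drift by more than that. Visit windows and the handling of actual visit days are commonly left to a fuller protocol or analysis plan. Phase A follow-up is almost complete, so new target dates would change little there.

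Most of this stands and limits the size of the point. It does not remove the contradiction. Random drift adds noise, whereas a discharge origin adds a shift linked to treatment and complications. The schedule figure is not shown, but it could not make two conflicting sentences agree.

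A reader might infer more than the article supports:

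- **Loss from the intention-to-treat set.** A patient who never has surgery has no postoperative discharge from which to schedule visits. The missing-data section nevertheless keeps all randomized participants in the analysis and imputes the primary outcome. Such a patient has no surgery date either, so the gap is not peculiar to the discharge origin.
- **Unequal time bases for QALYs.** The cost-effectiveness plan computes the area under the curve from utility and its matching duration, and the surgery and discharge dates are collected. Nothing says nominal visit times would be used.
- **A contradiction over the in-hospital questionnaire.** The abstract lists "baseline, postoperative day 1, weeks 3, 7, 12, months 6, 12, 18, 24", while the Hospital stay section says "Prior to discharge, participants will complete the Trial Health Questionnaire". With a median stay of 4 days, postoperative day 1 normally falls before discharge, so both can be true.
- **A material bias.** This needs a gap between arms of two days or more, or long complicated stays concentrated in one arm. The article gives neither.

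**Conclusion.** The point holds as an inconsistency on the primary time point, with a poor choice of origin in the follow-up section and a small expected consequence. Discharge is a post-randomization event expected to differ by arm, so it should not set the assessment clock when the objective is stated from surgery.

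On the article's figures, the discharge origin moves the week-12 score by about 4 to 6 days in both arms and separates the arms by 0 to 0.4 day. The resulting bias is 0 to 4% of the MID at week 3 and at most 1.6% at week 12. Any bias runs against RTS. These sizes rest on the assumed recovery slopes, on utility still rising at the visit, and on the trial's stays resembling those quoted. A larger gap between arms would be a further assumption. The article gives no basis for saying that the primary result is materially biased.

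**What to change.** Reconcile the Primary objective and Follow-up assessment sections. Time every EQ-5D-5L assessment from the date of surgery, or from randomization where no surgery takes place, and state the same origin in the Primary outcome section and Table 3.

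For Phase A data already collected, use actual days since surgery in the analysis, at least as a sensitivity analysis. A longitudinal model with actual days as the time axis, with the arms compared at day 84, is preferable to adding visit day as a covariate at a single visit. Under the discharge rule, visit day carries length of stay, so adjusting for it would condition on a post-randomization outcome.

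The cost is a few lines of protocol text and target dates that move by a few days. Surgery and discharge dates are already recorded. The gain is mostly in Phase B, which is still recruiting towards 592 patients with completion expected at the end of 2031.
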